### Participant inclusion and exclusion criteria

Mothers of Mexican descent, along with their preschoolers between the age of 3 and 5 years old enrolled in participating childcare centers are eligible for the study. Preschoolers.

### Participant recruitment

Participants will be recruited through meetings, flyers, and take-home letters. Interested parents will be screened for study eligibility and informed consent will be obtained prior to data collection.

### Intervention

The intervention “Healthy Change” is informed by the Social Cognitive Theory (SCT) [24]. SCT describes human behavior as a dynamic and reciprocal interaction of personal factors, behavior, and the environment [24]. Based on the SCT, Healthy Change intervention strategies focus on cognitive and behavioral skills to enable mothers to take actions in managing their child’s weight. The application of Social Cognitive Theory Concepts is shown in Table 1. The Healthy Change intervention curriculum consists of four sessions: 1) Understanding excess weight and obesity as a health problem and current and future health consequences; 2) How is my child’s weight?; 3) Maternal feeding styles and physical activity; and 4) I can!, which includes strategies to management child’s health behaviors.

**Table 1 Tab1:** Social Cognitive Theory (SCT) Concepts and Components of “Healthy Change” Intervention Group

Concepts of SCT	Intervention strategies
Reciprocal determinism: explore personal and environmental factors that can contribute to the change of cognition and behavior.	-Investigate the maternal beliefs related to OW-OB -Etiology of obesity: genetic factors and environmental -Present and future health effects of OW-OB -Recognize signs indicating that a child is OW-OB -Image perceived vs actual image
Self – efficacy: Increase Self-efficacy to manage child’s life style behaviors related to weight. Modeling - learning by observation	- Explore achievements that have been reached in management child’s life style behaviors related to weight and techniques which could be generalized as desired behaviors. - Ask the mother to comment an attempt which failed and explore individual and environmental factors that might have contributed in this attempt failed. - Teaching strategies of calm moment and time out. - Ask the mother that practice strategies and provide feedback
Behavioral capacity: providing opportunities for the mother to master necessary skills	- Together, identify actions that can be performed to manage child’s life style behaviors related to weight.
Reinforcement: Increase the expectations of outcomes’ behavior Reinforcing positive behaviors.	- Together, identify maternal feeding style and feeding practices of the participating mothers. - To identify factors of which contribute to the increase of child’s weight. - Teaching the participating mother practices that contributes to a healthy child’s weight.

Attention control is considered a valid control condition when conducting trials of social-behavioral interventions such as Healthy Change. We developed an attention control curriculum with a similar dose of group education entitled: *“Hygiene and Health Promotion”*. The four weekly group sessions cover the following topics: 1) The mother as her child’s hygiene promoter; 2) Hygiene and food safety at home; 3) Best ways to store food in your kitchen; and 4) Accident prevention at home and surrounding areas.

Each session for both groups will last about 90 min and will be held in a room within the participants’ own childcare institution. Both the Healthy Change and Hygiene and Health Promotion curriculum are available in two languages, Spanish and English. In Mexico, the content is delivered in Spanish. In the USA, mothers select the language of their preference for group education.

### Procedure to implement the intervention

The Healthy Change study uses a train-the-trainer model for intervention delivery. Each research site director is responsible for identifying and recruiting Promotoras from the participating childcare centers. To qualify, a Promotora must have a child enrolled at the participating childcare center. Promotora training includes 6 h of face-to-face training on the overall study, each session’s content, take home activities, and interpersonal communication skills. Promotoras take and must pass a certification exam in order to qualify for delivering the parent sessions. If she does not pass the exam, she will receive remediation and will be asked to retake the exam. Promotoras who do not pass the exam on the second attempt will not qualify to serve as Promotoras for the study.

The intervention includes Promotora-led sessions held in the classroom. Promotoras will use an English or Spanish facilitator guide to deliver the content. Promotoras have access to a projector and screen, whiteboard and markers or chalk, pencils, sheets and participant rosters.

### Evaluation methods

#### Process evaluation

Process evaluation of the intervention will include multiple data sources including, but not limited to, session duration, attendance, and context. Research personnel will observe a random group education session to assess delivery using a Healthy Change Fidelity Checklist. Focus groups will be conducted with up to 12 participating mothers in the intervention group at each research site at the end of the intervention. Program participants will be invited to participate in these group discussions on the day of the endpoint questionnaire. At least one focus group will be held at each participating center. An external experienced moderator along with a co-facilitator will use a semi-structured interview guide to facilitate each focus group. All focus group meetings will be audio-recorded and transcribed verbatim. The recordings will be transcribed and imported into NVIVO software for analysis [25].

#### Outcome evaluation

Baseline and post-intervention data will be collected on all participants. Each mother will receive 25 USD at the end of the intervention for their participation in the data collection. The primary outcome of this study is the proportion of mothers who accurately estimate their children’s weight status. Maternal perception of child’s weight is measured using the Parents’ Perceptions about Their Child’s Appearance and Health Questionnaire [19]. Mothers are asked to indicate their child’s weight status from 5 response options: “underweight”, “a little underweight”, “about the right weight”, “a little overweight”, or “overweight” (MPCW by words). Mothers also checked one of the body sketches (MPCW by image) in the age range 2 to 5 years old [19, 26].

Secondary outcomes include:Change in the maternal feeding styles. Maternal feeding styles is measured using the Caregiver Feeding Style Questionnaire. The questionnaire consists of 19 questions grouped in two dimensions: demandingness and responsiveness. Subsequent calculation of the median of both dimensions places participants in one of the four styles, i.e., authoritative, authoritarian, indulgent, or uninvolved [16].Increased self-efficacy score of maternal influencing on children’s health behavior. Mothers rate their confidence on a 5-point Likert scale ranging from “strongly disagree” to “strongly agree” on these two statements: “I can influence my child’s food choices” and “I can influence my child’s amount physical activity” [27].Improved score of family nutrition and physical activity. The Family and Nutrition and Physical Activity (FNPA) screening tool is used to assess mothers’ practices that may predispose children to becoming overweight [28]. The FNPA tool consists of 20 questions assessing family meals, family eating practice, food and beverage choices, material feeding restriction/ reward practice, child’s screen and activity time, sleep schedule, family activity routine and healthy environment [28]. Each question has four options: i.e., “Never/Almost Never”, “Sometimes”, “Often”, and “Very Often/Always” [28].Reduction or maintenance of the child’s BMI and BFP: The child’s weight is measured by Seca Scale 813 and height by Seca stadiometer 214, the BFP is measured by bioelectrical impedance by InBody 230.

Maternal BMI is assessed as a medicating factor. The maternal weight is measured using Seca scale 813 and the height with stadiometer SECA 214. Subsequently, the maternal BMI is calculated and classified as: low weight (< 18.5), normal weight (18.5–24.9), pre-OB (25.0 to 29.9), OB I (30.0–34.9), OB II (35.0–39.9) and OB III (> 40) [29]. Maternal body fat percentage (BFP) will be measured by bioelectrical impedance by InBody 230.

A self-administered questionnaire is used to collect socio-demographic data, e.g., age, education level, marital status, monthly family income and child’s age and sex, as well as degree of acculturation using the Scale of Acculturation of the Hispanic for participants in Texas, USA [30].

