**Methods/Design:**

The “Healthy Change” is a multicenter two-arm randomized trial in four centers. Three centers are in Mexican States (Nuevo Leon, Tamaulipas, and Zacatecas). The fourth center is in San Antonio, Texas, USA. A total of 360 mother-child pairs (90 pairs per center) are to be randomly and evenly allocated to either the intervention or the control group. Intervention group will receive four-session group obesity prevention education. Control group will receive a four-session personal and food hygiene education. The education is delivered by trained peer-mother promotoras. Data will be collected using questionnaires and focus groups. The primary outcome is a change in proportion of mothers with accurate MPCW. Secondary outcomes include change in maternal feeding styles and practices, maternal self-efficacy and actions for managing child excessive weight gain.

McNemar’s Test will be used to test the primary outcome. The GLM Univariate procedure will be used to determine intervention effects on secondary outcomes. The models will include the secondary outcome measures as the dependent variables, treatment condition (intervention/control) as the fixed factor, and confounding factors (e.g., mother’s education, children’s gender and age) as covariates. Sub-analyses will be performed to compare intervention effects on primary and secondary outcomes between the samples from Mexico and Texas, USA. Qualitative data will be analyzed through analysis of inductive content. A combined coding model will be developed and used to code transcripts using the NVivo software.

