### Trial design

The “Healthy Change” study is a multicenter two-arm randomized trial with four research sites, three in Mexico: a) Nuevo León, b) Tamaulipas, and c) Zacatecas, and one in San Antonio, Texas, USA. At each site, two childcare centers are randomly assigned to either the intervention or the attention control group. A total of 360 pairs of preschoolers and their mothers, i.e., 90 pairs per site, are recruited for the trial. Intervention participants will receive a four-weekly group education focusing on maternal perception of children’s bodyweight that facilitate healthy behavioral changes for the family. Control participants will receive a four-session group education on food hygiene and first aids as attention control. The outcomes include change in the proportion of mothers who accurately estimate their children’s weight categories, change in feeding style, maternal self-efficacy and actions taken in managing the child’s excessive weight gain. Data are to be collected at baseline and the end of the four-week group education from both groups. The study began on 08–29-2015, and will end on 11–20-2018.

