### Sample size and statistical power

The primary outcome of this intervention will be the proportion of mothers who adequately estimate their child’s weight status. Assuming the intra-class correlation coefficient (ICC) of 0.03, to detect a change of mother’s accurate estimation of children’s weight status from 50 to 70% with 80% power, 37 mother-child pairs would be required per research center per arm [23]. Accounting for a 15% attrition rate, each research site will enroll 45 pairs of mothers and children for the intervention and another 45 pairs for the control group. The total sample size for this four-center trial will be 360 pairs of mothers and children.

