#### Healthy change intervention effect

The quantitative data will be analyzed in Statistical Package for the Social Sciences (SPSS) version 23. WHO Anthro (version 3.2.2, January 2011) and macros will be used to calculate children’s age- and gender- specific BMI percentile and children will be classified by the World Health Organization | BMI-for-age chart: malnutrition (percentile < 3), low weight (≥3 and < 15), normal weight (≥15 and < 85), OW (≥85 but < 97), and OB (≥97) [31]. The rate at which mothers accurately classify their children’s weight status will be calculated in two ways, i.e., by words or by images. Accurate MPCW by words will be defined as show in Table 2.

**Table 2 Tab2:** Accurate MPCW by words

Children’s actual weight status by BMI percentile	MPCW by words
Malnutrition (< 3 percentile) Low weight (≥ 3 and < 15 percentile)	“underweight” or “a little underweight”
Normal weight (≥ 15 and < 85 percentile),	“Normal weight”
Overweight (≥ 85 but < 97 percentile)	“A little overweight”
Obese (≥ 97)	“Overweight”

With regard to the MPCW by image test, an accurate perception is defined when mothers of underweight and normal weight children select an image smaller than the average image or when mothers of children with OW-OB select the average or a larger image.

McNemar’s Test will be used to test the primary outcome measure, i.e., intervention effect on change in proportion of mother’s accurate recognition of their preschooler’s weight status. The GLM Univariate procedure will be used to determine intervention effects on secondary outcomes e.g., scores of mother’s self-efficacy, feeding practices and children’s BMI percentiles and fat%. The models will include the secondary outcome measures as the dependent variables, treatment condition (intervention versus control) as the fixed factor, and confounding factors (e.g., mother’s education level, children’s gender and age) as covariates. Sub-analyses will be performed to compare intervention effects on both primary and secondary outcomes between the samples from Mexico and Texas, USA.

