## Discussion

Childhood OB is one of the most serious public health issues of the twenty-first century. Children with OB are at increased risk of obesity as adults and are more likely to develop chronic health conditions, such as diabetes and cardiovascular disease, at a younger age. It is therefore necessary to implement strategies from childhood to prevent and treat OW-OB paying special attention to parents, given that they not only act as behavior moderators, but also are responsible for the quality and quantity of food made available to their children. When parents are involved in interventions to prevent and treat weight problems in their children, there are more possibilities of achieving satisfactory outcomes.

The pilot study aims at correcting Mexican mothers’ misperception of their children’s weight status as the initial step of obesity prevention. Studies conducted in countries such as the USA, Italy, United Kingdom, Germany and Malaysia have assessed MPCW and found that the majority of mothers of children with OW-OB have misperceptions of their child’s weight, and they underestimate it; this misperception could have impact in other parenting strategies related to feeding and physical activity of their child. On the other hand, only one study conducted in Iran documented the impact of an educational intervention on maternal perception of her child’s OB in scholar age; therefore, we conduct this research to evaluate the feasibility and effect of “Healthy Change” intervention on MPCW of her pre-school child, through accuracy MPCW post intervention.

This collaborative research endeavor can produce promising outcomes, enabling the team to secure extramural funding for a large-scale randomized controlled trial. The innovative research inquiry will advance our knowledge of employing effective culturally appropriate prevention strategies to curb the childhood obesity epidemic facing both the United States of America and Mexico.

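### The primary outcome is worded both as the proportion of accurate mothers and as the change in that proportion, and the contrast between arms is never stated

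*Protocol article*

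**What the plan says.** Two sections of the protocol article give the primary outcome as a proportion, with no time point and no contrast:

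- Sample size and statistical power: "The primary outcome of this intervention will be the proportion of mothers who adequately estimate their child’s weight status".
- Outcome evaluation: "The primary outcome of this study is the proportion of mothers who accurately estimate their children’s weight status".

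Two sections give it as a change:

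- Abstract, Methods/Design: "The primary outcome is a change in proportion of mothers with accurate MPCW".
- Healthy change intervention effect: the tested quantity is the "intervention effect on change in proportion of mother’s accurate recognition of their preschooler’s weight status".

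Two further places bear on the point. Trial design lists the change first, without calling it primary: "The outcomes include change in the proportion of mothers who accurately estimate their children’s weight categories". The Discussion says that the effect will be evaluated "through accuracy MPCW post intervention".

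The planned test is stated once in the body of the article: "McNemar’s Test will be used to test the primary outcome measure". The covariate models in the same section are for secondary outcomes. Outcome evaluation says that baseline and post-intervention data are collected on all participants.

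**The concern.** Once two arms are compared, a proportion and a change in proportion lead to different estimates. The first compares the arms after the education. The second also subtracts the difference between arms at baseline. With 360 individually randomised mothers that baseline difference would usually be modest. Here Trial design randomises two childcare centres at each of four sites, so each arm rests on about four centres, and chance imbalance can be appreciable.

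If the article does not say which comparison is primary, the choice can be made after the baseline imbalance is known. Neither reading makes the best use of the baseline measurement. An unadjusted post-intervention comparison carries any chance imbalance into the result, and an unadjusted change over-corrects for it when the correlation between the two measurements is well below one.

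**Working it through.** **Inputs from the article.** Sample size and statistical power: 37 mother-child pairs per site per arm after attrition, ICC 0.03, 50% to 70%, 80% power. Trial design: four sites, one childcare centre per arm at each. Analysed mothers per arm: 4 × 37 = 148. Design effect: 1 + (37 − 1) × 0.03 = 2.08.

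**The plan's own figure.** Treat 50% and 70% as two independent proportions with unpooled variance 0.50 × 0.50 + 0.70 × 0.30 = 0.46.

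- One-sided 5%, 80% power: (1.645 + 0.842)² × 0.46 / 0.20² = 71.1 per arm. Then 71.1 × 2.08 / 4 = 36.97, which rounds up to the stated 37.
- Two-sided 5%: 90.3 × 2.08 / 4 = 46.9.

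The article states neither alpha nor sidedness. A two-sided McNemar calculation also comes to about 36 if a within-mother correlation of 0.3 is assumed. The sample size therefore does not reveal which comparison was intended.

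**Gap between the two readings.** Write P for the proportion accurate, T and C for the arms, and 0 and 1 for baseline and post.

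- Post-intervention reading: P_T1 − P_C1.
- Change reading: (P_T1 − P_T0) − (P_C1 − P_C0).
- The first minus the second is P_T0 − P_C0, the baseline difference.

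Its expected value is zero under randomisation, so both readings estimate 20 points on average at the design effect.

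**Size of the gap at 50% baseline accuracy.** Variance per mother is 0.50 × 0.50 = 0.25. The article does not say how the ICC of 0.03 divides between sites and childcare centres, so both ends are shown.

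| Where the ICC lies | SD of baseline difference | Share of trials with a gap above 10 points |
|---|---|---|
| Wholly between sites, removed by randomising within site | √(2 × 0.25 / 148) = 5.8 points | about 9% |
| Wholly between childcare centres | √(2 × 0.25 × 2.08 / 148) = 8.4 points | about 23% (normal approximation), about 24% (simulation) |

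For scale, the standard error of the unadjusted post-intervention difference is √(0.46 / 148) = 5.6 points in the first case and √(0.46 × 2.08 / 148) = 8.0 points in the second. The SD of the gap is thus about one standard error in either case.

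**How often the verdict would differ.** This needs two quantities that the article does not give: the correlation between a mother's two answers, and the correlation of centre effects over time. Simulations used four unpaired centres per arm, 37 mothers each and ICC 0.03, and assumed a latent within-mother correlation of 0.3 to 0.7. At the design effect, the two readings disagreed on significance in 33–42% of trials with a test on centre means, and in 17–20% with a mother-level test that ignores clustering. With no true effect, the figures were about 9% and 21–23%. With the centre-level ICC set to zero, disagreement at the design effect fell to 22–27% and 9–15%.

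**Precision.** A separate simulation of the same layout assumed within-mother correlation 0.2 to 0.6 and centre-effect correlation over time of 0 or 0.8. The SD of the estimated effect was 7.9–8.0 points for the post-intervention difference, 6.5–11.0 for the difference in change, and 5.8–7.9 with adjustment for baseline accuracy.

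**The case against.** The strongest reply is that this is loose wording and not two rival endpoints. The sample size section follows its definition with the aim "to detect a change of mother’s accurate estimation of children’s weight status from 50 to 70% with 80% power", the abstract and the analysis section both speak of change, and so do the aims. The sections that give a proportion may simply be naming the measure. The Discussion clause that points to post-intervention accuracy is not an endpoint definition. This stands in part: the text leans towards change, and a reader who infers that the article defines a post-only endpoint goes beyond what it says. But leaning towards change does not settle the matter. A change within mothers and a difference in change between arms are not the same thing, and the named test supplies only the first.

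A second reply is that the real defect is the missing between-arm contrast, so that stating it would settle the wording too. That is largely right, and the fix below does both together. The definition still has to be chosen, because a between-arm test could be applied to either quantity.

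A third reply concerns size. Randomisation is within site, between institutions chosen to be similar, so the 8.4-point figure is the upper end of a range. That is accepted, and the range is given. It is also fair that choosing covariates for the primary model is commonly left to an analysis plan that is not shown. Baseline adjustment is therefore offered as an improvement, not as a missing element. At low within-mother correlation it gains almost nothing over the post-intervention comparison.

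**Conclusion.** The inconsistency is in the current text and no section resolves it. The primary outcome is a proportion in two sections and a change in two others, and the between-arm contrast is not stated anywhere. The consequence is a chance gap between the two estimates with an SD of about 5.8 to 8.4 points, exceeding 10 points in about 9% to 24% of trials, against a target of 20. These figures rest on the article's 37 per centre, ICC of 0.03 and 50% baseline accuracy, with two childcare centres per site. The article allows a third centre if recruitment falls short, which is not modelled here.

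Three stronger conclusions might be inferred, and the document does not support them. The inconsistency does not bias the trial, because both readings have the same expectation under randomisation. The baseline difference between arms is not bound to be large: by the figures above, about 76% to 91% of trials fall within 10 points. And no rate at which the two readings reach different conclusions can be stated as fact, because it depends on correlations that the article does not give.

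**What to change.** Use one definition in the abstract, Trial design, Sample size and statistical power, Outcome evaluation and Healthy change intervention effect. Suggested wording:

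> The primary outcome is whether the mother accurately classifies her child's weight status at the end of the four-week education. The effect is the between-arm difference in this proportion, adjusted for the mother's own baseline accuracy, in an analysis that accounts for site and childcare centre.

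Keep the within-arm change from baseline, with McNemar's test, as descriptive only. The analysis section computes accuracy both by words and by images, so the same sentence should also name which of the two is primary.

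The cost is wording plus one covariate that is already collected, with no added participants or visits. The one drawback is that the headline result is no longer a simple before-and-after change.
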